## Abstract

**Introduction::**

Human Immunodeficiency Virus (HIV) infection remains prevalent co-morbidity, and among fracture patients. Few studies have investigated the role of exercise interventions in preventing bone demineralization in people who have fractures and HIV. If exercise exposed, HIV-infected individuals may experience improved bone health outcomes (BMD), function, quality of life (QoL). The study will aim to assess the impact of home based exercises on bone mineral density, functional capacity, QoL, and some serological markers of health in HIV infection among Nigerians and South Africans.

**Methods and design::**

The study is an assessor-blinded randomized controlled trial. Patients managed with internal and external fixation for femoral shaft fracture at the study sites will be recruited to participate in the study. The participants will be recruited 2 weeks post-discharge at the follow-up clinic with the orthopaedic surgeon. The study population will consist of all persons with femoral fracture and HIV-positive and negative (HIV-positive medically confirmed) aged 18 to 60 years attending the above-named health facilities. For the HIV-positive participants, a documented positive HIV result, as well as a history of being followed-up at the HIV treatment and care center. A developed home based exercise programme will be implemented in the experimental group while the control group continues with the usual rehabilitation programme. The primary outcome measures will be function, gait, bone mineral density, physical activity, and QoL.

**Discussion::**

The proposed trial will compare the effect of a home-based physical exercise-training programme in the management of femoral fracture to the usual physiotherapy management programmes with specific outcomes of bone mineral density, function, and inflammatory markers.

## Introduction

1

South Africa, with an estimated population of 56.5 million in 2017^[1]^ is the epicenter of the HIV epidemic in the world.^[2]^ According to the UNAIDS ^[3]^ report, South Africa has an estimated 7.5 million people living with HIV, with 200,000 new infections and 72,000 HIV-related deaths. Currently, South Africa has the most extensive antiretroviral treatment (ART) programme globally, with over 3 million HIV-infected persons.^[2]^ HIV programmes in SA are estimated to cost $1.34 billion annually.^[4]^ Similar to South Africa, Nigeria, with an estimated population of 161.7 million by 2015,^[5]^ has about 3.2 million people living with HIV.^[4]^ Currently, Nigeria records about 180, 000 HIV-related deaths, 227, 000 new HIV cases with the highest incidence occurring in the productive age group (15–49 years).^[4]^ In Nigeria, 51% of adults with HIV are placed on antiretroviral therapy (ART).^[6]^ Highly active antiretroviral therapy (HAART) has significantly increased life expectancy.^[7,8]^ With increased longevity and side effects of HAART, the prevalence of chronic and non-communicable diseases among people living with HIV as part of the ageing process, has been evident.^[9]^

Reduced bone mineral density is a common associated with HIV, and their relationship is multi-factorial. The major related pathogenesis is that HIV infection alters bone metabolism, and this is further compounded with long-term use of HAART.^[10–12]^ HIV was shown to increase the risk of osteoporosis by 3.7, and the long-term use of HAART further increases the risk by 1.6 when the prevalence of osteoporosis was compared between HIV-positive and HIV-negative individuals.^[13]^ Although, the loss of bone mineral density associated with the use of HAART usually stabilizes after one year, and there is no further HAART related bone loss.^[14]^

Apart from HIV and several other risk factors for reduced bone mineral density, immobilization as a result of fracture is also a predisposing factor. A study by Ceroni et al,^[15]^ showed that there is a significant reduction in bone mineral density in patients immobilized using cast compared to healthy controls. The difference in bone mineral density ranged from −5.8% to −31.7% at the hip, greater trochanter, calcaneus, and total lower limb. Also, the consequent immobilization of the affected individuals should translate to loss of independence in activities of daily living, limited functional capacity, loss of economic independence and poor quality of life (QoL).^[16]^ These challenges could minimize functional mobility with an adverse impact on socialization resulting in restricted social participation. The net effect from a population-based national outlook suggests a substantial loss of productive workforce, decline in the overall national productivity, economic development, gross domestic product, and QoL with a predictable negative impact on poverty level.^[17,18]^ Therefore, any interventions that could prevent/ameliorate or reverse the adverse effects of HIV and HAART-related bone demineralization should be of socio-economic significance.

Physical exercise can be defined as (a subset of physical activity) planned, structured and repetitive bodily movement, performed with the goal of improving or maintaining physical fitness.^[19,20]^ Not only does exercise improve health, it also increases muscle strength, coordination, balance, flexibility, and leads to overall health, which may enhance functional capacity in activities of daily living and thus, QoL. Available evidence suggests that exercise is a safe and relevant therapy in HIV/AIDS management, but its safety and relevance have not been fully investigated or exploited to the benefit of the patients.^[21–23]^ The decision on whether to use physical exercises to address the issues related to bone health in HIV conditions should be guided by objective clinical markers. In recent years, biochemical markers (Bone-specific alkaline phosphatase and pyridinoline) have enabled the detection of changes of bone turnover in response to biological (e.g., hormonal), biomechanical, and other variables.^[24,25]^ This trend is useful and may guide therapeutic/clinical decisions for the benefit of clients.

We previously described a home-based rehabilitation (HBR) programme we developed in KwaZulu-Natal, South Africa, which adhered to the fundamental principles of a theoretical model of integrated care, that is, the Chetty model, and is also home-based.^[26]^ The Chetty model promotes greater integration and collaboration between hospitals and communities. The HBR programme in KwaZulu-Natal was able to apply several principles such as evidence-based practice, task shifting to lay personnel, enabling patient-centered care and maximising function and independence of People Living with HIV/AIDS (PLWHA). Other elements, such as the adoption of a multidisciplinary approach, training on the use of disability screening tools and the use of evidence to influence policy development were more challenging to implement. However, our findings suggest that it is possible to implement elements of the integrated model of care. The lessons we learned from our KwaZulu-Natal study,^[26]^ and the Nigeria-HIV BMD study,^[27]^ have been explored to determine how the home-based exercise programmes can be deployed to address bone health issues and other contextual disabilities arising from HIV that may be amenable to physical exercises. Also, the small sample studies already cited have demonstrated efficacy and relevance of physical exercises in ameliorating/preventing HIV/HAART-related bone demineralization, while boosting immune function, and serves as an orientation towards a population-based study.^[27–29]^ We will also exploit the opportunity to explore various coping mechanisms of people living with HIV using an adaptation of the COPE questionnaire, which may have implications for QoL.^[30]^ The objective of this article is to describe the protocol of a study, which is aimed at determining the effects of exercise on bone mineral density and other health outcomes. The proposed study design is randomized controlled trial, as outlined in Figure 1.

**Figure 1 F1:**
[figure not shown]
Modified anticipated CONSORT flow diagram for a single-blind randomised controlled trial of physical exercise intervention for bone health in the patients.

## Aim and objectives of the study

2

The study will aim to determine the effectiveness of a home-based exercise programme in the management of femoral fracture. The specific objectives of the study will be to:

1.To develop an evidence-based exercise intervention programme, based on evidence from the literature for improved: BMD, immune and inflammatory markers, BMI, function capacity and HRQOL2.To determine the effects of physical exercises on BMD, immune and inflammatory markers and functional capacity in adults living with HIV in Nigeria & South Africa with femoral shaft fracture.

## Hypothesis

3

It is hypothesized that:

1.Home based exercise programme will significantly influence muscle strength, gait output/speed, BMD, functional capacity, body composition (%BFM, FM, FFM, and BMI) and immune function (CD^4+^ count) in HAART-experienced HIV-infected adults compared to controls in both Nigeria and South Africa.2.HAART may have a significant interaction effect with physical activity to improve BMD in HAART-experienced HIV-infected adults compared to controls in Nigeria and South Africa.

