### Phase two

5.2

The second phase of the study will aim to determine the effects of physical exercises on BMD, immune and inflammatory markers and functional capacity in adults living with HIV in Nigeria and South Africa with femoral shaft fracture.

*Trial design:* The proposed study design is a multi-center parallel group assessor-blinded randomized controlled trial with allocation ratio of 1:1.

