### Participant

5.6

*Sampling and sample size:* Consecutive sampling will be used to recruit the participants. Using the statistical superiority sample size design,^[34]^ a sample of size of 36 participants per group will be sufficient to show a statistical difference in the bone mineral density between the control and the experimental group. For this study, the groups are divided into four which are the experimental group (HIV+ and HIV−) and the control group (HIV+ and HIV−), therefore, at least a total of 144 patients per study site will be recruited to participate in the study. The sample size will be calculated using Equation 1:(1)$$N=2\times \left\{Z_{1-\alpha /2}+Z_{1-\beta }/d2\right\}\times Pooled\;SD$$

where N = total sample size per group, *Z*_1−α/2_ = 1.96, *Z*_1−β_ = 0.845, *d*^2^ = 0.1 and pooled standard deviation = 0.093.

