### Statistical analysis

5.15

Data to be collected shall include discrete and normally distributed continuous variables. The normal distribution of the continuous variables will be tested using the Shapiro–Wilk test, and depending on the outcome, parametric or non-parametric statistics will be used to analyze the data. The change in the categorical outcomes across the time points will be measured using the McNemar's test. The difference in the continuous outcomes between the groups will be measured using the independent *T*-test (parametric) and Mann–Whitney *U* test (non-parametric). Intention to treat analysis method will be used for this study. Alpha shall be set at *P* < .05 (two-tailed). All analyses will be intent-to-treat and missing data will be treated as missing.

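### Hypothesis 1 claims an effect in both countries, but the single between-group test has no country term and, if pooled, cannot support that claim

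*Protocol article*

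**What the plan says.** Four parts of the protocol article bear on this.

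- **Hypothesis (section 3).** Hypothesis 1 predicts that the home programme will influence BMD and other outcomes "in HAART-experienced HIV-infected adults compared to controls in both Nigeria and South Africa". Hypothesis 2 names the two countries without the word 'both'.
- **Sample size (section 5.6).** The article states that "a sample of size of 36 participants per group will be sufficient to show a statistical difference in the bone mineral density". It counts four groups (experimental and control, each HIV-positive and HIV-negative) and concludes that "at least a total of 144 patients per study site will be recruited to participate in the study". Section 5.3 defines Site 1 as Johannesburg and Site 2 as Enugu, so site and country coincide.
- **Design and objectives.** Section 5.2 describes a "multi-center parallel group assessor-blinded randomized controlled trial with allocation ratio of 1:1". Objective 2 in section 2 concerns effects on BMD, markers and "functional capacity in adults living with HIV in Nigeria & South Africa with femoral shaft fracture". Both treat the two countries as one trial.
- **Analysis (section 5.15).** "The difference in the continuous outcomes between the groups will be measured using the independent" t-test or the Mann-Whitney test, at a two-sided .05 level. Country, site and pooling are not mentioned. Section 5.8 names only HIV status as a block for allocation.

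**The concern.** The hypothesis and the sample size are framed country by country. The design label, the objective and the test are framed for one combined trial. A pooled test addresses whether the average effect over the two countries differs from zero, and a large effect in one country can make it significant by itself. If that result is reported against Hypothesis 1 as worded, benefit will be claimed for a country in which there may be none.

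The article itself gives reasons why effects might differ. The control treatment is usual rehabilitation as each clinic delivers it (section 5.4), and the Discussion says that contextual and racial differences may influence the effect of exercise on BMD.

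There is a smaller loss as well. An unadjusted two-group test leaves any difference in outcome level between the countries in the error variance.

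**Working it through.** **Inputs.** From section 5.6: 36 per group, four groups, Z values 1.96 and 0.845, an effect term printed as d² = 0.1, and "pooled standard deviation = 0.093". From section 5.15: two-sided .05. From section 5.3: two sites, one per country.

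**The plan's own figures.**
- 4 × 36 = 144 per site, as stated.
- Z = 0.845 corresponds to a power of 80.1%.
- The 36 does not follow from the printed inputs. With a difference of 0.1 and SD 0.093, the usual formula gives 2 × (1.96 + 0.845)² × 0.093² / 0.1² = 13.6, or 14 per group. That is a separate problem and this point does not need it. It does mean that the intended effect is uncertain, so two effect sizes are carried below.

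**Population.** Hypothesis 1 concerns HIV-positive adults, so each country contributes 36 per arm and the pooled comparison has 2 × 36 = 72 per arm. Power is from the noncentral t distribution with noncentrality δ√(n/2), where δ is the standardised difference and n the number per arm.

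**Two effect sizes.**
- A: δ = 0.67, the value that gives 80% power at 36 per arm. This is an assumption and is not stated in the article.
- B: δ = 0.1/0.093 = 1.08, if the printed 0.1 is the difference itself.

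**Benefit in one country, none in the other.** With equal country sizes, the pooled difference averages δ/2.

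| | A | B |
|---|---|---|
| Average δ | 0.335 | 0.54 |
| Chance that the pooled test (72 per arm) is significant | 51% | 89% |

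These percentages are how often the trial would be in a position to make the claim for both countries. Given that one country has no effect, the claim is false every time it is made.

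**Requiring significance in each country.** The countries are independent, so joint power is the square of per-country power.

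| | A | B |
|---|---|---|
| Power per country (36 per arm) | 80% | 99.4% |
| Joint power | 0.80² = 64% | 0.994² = 98.9% |

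**One illustration (chosen differences, SD 0.093).** Suppose that the observed differences are 0.06 in one country and 0.02 in the other. The standard error per country is 0.093 × √(2/36) = 0.0219, which gives p = 0.008 and p = 0.36. The pooled difference is 0.04 with standard error 0.093 × √(2/72) = 0.0155, which gives p = 0.011. The pooled test succeeds, and a claim for both countries is not supported.

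**Precision.** If mean outcome levels differ between countries by D within-country SDs and the countries are equal in size, the variance used by an unadjusted test is inflated by 1 + D²/4. For assumed D = 0.5 this is 1.06, and for D = 1 it is 1.25. Stratifying or adjusting removes this inflation.

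**The case against.** The strongest reply is that this is a condensed article without its analysis plan. Pooling of centres, adjustment for country and subgroup reporting are commonly left to that plan. The text also leans towards pooling, and 'both' may simply describe where the trial runs.

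Much of this stands. The lack of a country covariate would not by itself be a finding, and pooling is the more natural reading of the design, objective and test. But an unseen plan that chose pooling would still conflict with Hypothesis 1 as worded, and the hypothesis and the basis of the sample size belong to this document. If 'both' is loose wording, a one-line correction settles it.

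Three stronger readings are tempting and should not be drawn.
- **Inflated type I error.** A reader might infer that each country will be tested and either one will count. No section suggests that rule, and the wording of Hypothesis 1 runs against it. A single pooled test keeps its 5% level.
- **A trial underpowered at 64%.** That figure depends on an effect worked back from 80% power at 36 per arm. With a difference of 0.1 and SD 0.093, joint power is about 99%.
- **Claims that are false half the time.** The 51% is the chance of a significant pooled result when one country has no effect. In that situation the claim for both is always false.

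**Conclusion.** The point holds as a mismatch between the claim, the basis of the sample size and the test. A pooled, unadjusted comparison cannot establish Hypothesis 1 as worded. With benefit in one country only, it would be significant about 51% of the time at an assumed 0.67 SD and about 89% of the time at 1.08 SD. Both figures assume 36 HIV-positive patients per arm in each country, equal variances and a null effect in the other country. The article does not show that effects will differ between the countries, only that they could. The loss of precision depends on how far outcome levels differ, which the article does not state. The correction is worth making because it changes what the trial can validly conclude at almost no cost.

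**What to change.** 1. In section 5.15, specify the between-arm comparison in HIV-positive participants, the population that Hypothesis 1 names, pooled over the two countries, stratified by or adjusted for country, and tested at two-sided .05.
2. Report the difference in each country with a 95% confidence interval, and the arm-by-country interaction, as exploratory.
3. Reword Hypothesis 1 so that the effect is claimed across participants in Nigeria and South Africa.
4. If a claim for each country is to stay, require significance in each. State the joint power as the square of the per-country power under the effect that the sample size is meant to detect: 64% if per-country power is 80%, about 99% if the difference is 0.1 and the SD 0.093.

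Under items 1 to 3 the cost is wording in sections 3 and 5.15 and one more term in the analysis, with no extra patients or data. The small downside is that the trial makes no confirmatory claim for each country separately.

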### Eligibility criteria

5.4

The study population will consist of all persons with femoral fracture and HIV-positive and negative (HIV-positive medically confirmed) aged 18 to 60 years attending the above-named health facilities. For the HIV-positive participants, a documented positive HIV result, as well as a history of being followed-up at the HIV treatment and care center.

Inclusion criteria

Only patients between 18 and 60 years at the last birthday and not more than 60 years at the next birthday.For HIV-negative participants, willingness to accept HIV testing.All patients on ART therapy with femoral shaft fracture will be recruited.All patients with lower limb fractures (femur) will be recruited.All patients must be ambulant.

Exclusion criteria

Severely ill persons based on investigator judgment.Presence of any bone or rheumatic disorder.Fracture of the femoral neck.

*Interventions*: The intervention programme will be a home-based exercise programme targeted at improving bone mineral density, function, gait, QoL, and physical activity. The intervention programme aims to improve the joint range of motion, gait training, muscle strengthening, and balance. The participants in the intervention group will be followed up weekly via phone calls to monitor the intervention and ensure adherence to the programme.

*Control group*: The control group will continue with their usual rehabilitation programme as conducted by the various clinics.

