### Allocation

5.8

Blocked allocation will be used to allocate the participants into groups. Random numbers will be generated to allocate the patients into intervention and control groups in blocks (10 numbers equally distributed into intervention and control groups). There will be two blocks namely

1.HIV-positive and2.HIV-negative blocks.

The number allocation will be done by independent research support. Opaque envelopes will be used to conceal the allocation.

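### Hypothesis 2 claims a HAART-by-exercise interaction on BMD, but the planned groups vary only arm and HIV status, and the stated tests do not estimate an interaction

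*Protocol article*

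**What the plan says.** - **Hypothesis (section 3), item 2:** "HAART may have a significant interaction effect with physical activity to improve BMD in HAART-experienced HIV-infected adults compared to controls", in both countries.
- **Participant (section 5.6):** "For this study, the groups are divided into four which are the experimental group" and the control group, each split into HIV-positive and HIV-negative. The plan is 36 per group and at least 144 per study site, sized for a BMD difference between control and experimental groups.
- **Allocation (section 5.8):** "There will be two blocks namely" HIV-positive and HIV-negative. HAART is not a stratification factor.
- **Eligibility criteria (section 5.4):** HIV-positive participants need "a documented positive HIV result, as well as a history of being followed-up at the HIV treatment and care center". Separate inclusion lines say "All patients on ART therapy with femoral shaft fracture will be recruited" and "All patients with lower limb fractures (femur) will be recruited".
- **Statistical analysis (section 5.15):** "The difference in the continuous outcomes between the groups will be measured using the independent" t-test, or Mann-Whitney U if the data are not normal. McNemar's test is named for change over time in categorical outcomes. No other test is named.

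**The concern.** An interaction between HAART and exercise is a statement about how the exercise effect changes with HAART. To separate it from HIV, one needs patients with and without HAART at the same HIV status, in both arms. The plan arranges no such contrast, and the hypothesis is itself confined to HAART-experienced adults.

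The protocol's own rationale makes the separation matter. The Introduction treats HIV and HAART as distinct contributors to bone loss, quoting a risk of osteoporosis raised by 3.7 for HIV and by a further 1.6 for long-term HAART. A HAART claim from this trial would merge the two.

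The word *controls* in Hypothesis 2 is also unclear. It could mean the randomised control arm or the HIV-negative patients, and these give different comparisons. As written, one of the two stated hypotheses has no matching test.

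**Working it through.** **1. What the groups can identify.** Consider a BMD model with an intercept, HIV, HAART, exercise, HIV × exercise and HAART × exercise: six terms. If every HIV-positive patient is on HAART and no HIV-negative patient is, the four groups give a design matrix of rank 4. The HAART column equals the HIV column, and the two interaction columns coincide. Adding HIV-positive off-HAART cells in both arms raises the rank to 6. The rank of 4 depends on the assumption that all HIV-positive patients are treated, which step 2 relaxes.

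**2. If some HIV-positive patients are off HAART.** The protocol gives no expected share, so it is an assumption here. With 72 HIV-positive patients per site split evenly by arm, the interaction detectable with 80% power, in SD units, is 2.805 × √(2/n_off + 2/n_on), where n is per arm.

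| Assumed share off HAART | n_off / n_on per arm | Detectable interaction |
|---|---|---|
| 5% | 1.8 / 34.2 | 3.0 SD |
| 30% | 10.8 / 25.2 | 1.4 SD |
| 50% | 18 / 18 | 1.3 SD |

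At 50% off HAART over two sites (144 HIV-positive patients) it is 0.94 SD. HAART would still be a non-randomised factor in each case.

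**3. What the named tests estimate.** A t-test between arms, with equal HIV strata, estimates the average of the two stratum effects. Effects of 0.05 and 0.05 (no interaction) and of 0.10 and 0 (interaction 0.10) both average 0.05. In a simulation with 72 per arm and SD 0.093, the arm t-test rejected in 89% of trials in the first case and 87% in the second. It does not tell them apart.

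**4. Size of interaction the trial can detect.** Inputs from section 5.6: z values 1.96 and 0.845 (sum 2.805), SD 0.093, 36 per group.

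- *The plan's own figure.* The standard formula with a difference of 0.1 gives 2 × 2.805² × 0.093² / 0.1² = 13.6, so 14 per group. Equation 1 read literally gives 2 × (1.96 + 0.845/0.1) × 0.093 = 1.9. A non-standard reading (0.1 squared, SD not squared) gives 146.3, near the 144 per site, but the protocol defines N as per group. The 36 is therefore not reproduced. That is a separate matter, and 36 is taken as given below.
- *Two-group difference.* SE = 0.093 × √(2/36) = 0.0219; detectable difference 2.805 × 0.0219 = 0.061 (0.66 SD).
- *Arm × HIV-stratum interaction, one site.* SE = 0.093 × √(4/36) = 0.031; detectable interaction 2.805 × 0.031 = 0.087 (0.94 SD).
- *Two sites pooled, 72 per cell (assumed).* SE = 0.093 × √(4/72) = 0.0219; detectable interaction 0.061.
- *Power at one site, Φ(interaction/0.031 − 1.96).* At 0.0615: Φ(0.02) = 51%. At 0.1: Φ(1.27) = 90%.

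**The case against.** **The HIV-positive group is not defined by ART use.** A reader might infer that Hypothesis 2 cannot be tested at all because HIV-positive and on HAART are the same thing here. The documents do not support that. Eligibility asks for a positive result and HIV-clinic follow-up, not current ART. The femur-fracture line carries no ART condition, and no exclusion removes untreated patients. The Introduction puts 51% of Nigerian adults with HIV on ART, although clinic follow-up may make the untreated share smaller in this trial. This objection stands against the absolute reading. It does not supply a designed contrast: untreated patients would enter by chance and without stratification.

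**If *controls* means HIV-negative patients, the two-by-two layout already answers the question.** This is partly right. The layout can support an interaction between arm and HIV status, and effect modification by a non-randomised baseline factor is a legitimate analysis. It is not, however, an interaction with HAART, and the stated tests would not estimate it.

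**An analysis plan not shown may add an interaction term.** It may, and that would meet the point about tests. It would not meet the point about groups and strata, which is a matter of design.

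**The power figures are selective.** A reader might infer that the trial is simply underpowered for any interaction. That is not established. The 51% rests on an effect of 0.061, back-solved from 36 per group, which the protocol never states. If the 0.1 in section 5.6 (labelled d²) is read as a BMD difference, an interaction of that size has about 90% power at one site.

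**Importance.** Hypothesis 2 is worded tentatively, and no interaction appears in the aims, the primary outcomes or the sample size. That limits the weight of the point but does not remove the mismatch.

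**Conclusion.** The point holds as a mismatch between a stated hypothesis and the stated design and tests. Following the protocol as written gives no valid test of a HAART-by-exercise interaction: HAART is neither a group nor a stratum, it would be largely confounded with HIV status, and the named tests do not target an interaction. How complete the confounding is depends on how many untreated HIV-positive patients enter, which the protocol does not say.

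The sizing was done for a two-group difference. An interaction must be √2 times as large (0.087 against 0.061 at 36 per cell) to be detected with the same 80% power. Whether that is a serious shortfall depends on the true interaction, which is not stated. The point deserves correction before analysis but does not threaten the main comparison of home programme with usual rehabilitation.

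**What to change.** - Reword Hypothesis 2: the effect of the home programme on BMD differs between HIV-positive (HAART-experienced) and HIV-negative patients. Drop the claim about HAART itself.
- Define *controls* as the randomised control arm.
- Add to section 5.15 a linear model for follow-up BMD with arm, HIV stratum, site and baseline BMD, plus an arm × HIV-stratum term as the test of Hypothesis 2. The protocol currently describes no such model, so this is a new model rather than one extra term in an existing one.
- Label the test secondary or exploratory. State that the sample size was not set for it, and give the detectable interaction (about 0.087 per site at SD 0.093 and 36 per cell).

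The cost is some redrafting and a small amount of extra modelling, with no change to recruitment or allocation. The sponsor gives up a HAART-specific claim that the planned groups were not built to support.
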